## Abstract

**Background:**

Exergames can provide encouraging exercise options. Currently, there is limited evidence regarding home-based exergaming in the postoperative phase of total knee replacement (TKR).

**Objective:**

This study aimed to investigate the effects of a 4-month postoperative home-based exergame intervention with an 8-month follow-up on physical function and symptoms among older persons undergoing TKR compared with home exercise using a standard protocol. In addition, a concurrent embedded design of a mixed methods study was used by including a qualitative component within a quantitative study of exergame effects.

**Methods:**

This was a dual-center, nonblinded, two-arm, parallel group randomized controlled trial with an embedded qualitative approach. This study aimed to recruit 100 patients who underwent their first unilateral TKR (aged 60-75 years). Participants were randomized to the exergame or standard home exercise arms. Participants followed a custom-made exergame program independently at their homes daily for 4 months. The primary outcomes at 4 months were function and pain related to the knee using the Oxford Knee Score questionnaire and mobility using the Timed Up and Go test. Other outcomes, in addition to physical function, symptoms, and disability, were game user experience, exercise adherence, physical activity, and satisfaction with the operated knee. Assessments were performed at the preoperative baseline and at 2, 4, and 12 months postoperatively. Exergame adherence was followed from game computers and using a structured diary. Self-reported standard exercise was followed for 4 months of intervention and physical activity was followed for 12 months using a structured diary. Qualitative data on patients’ perspectives on rehabilitation and exergames were collected through laddering interviews at 4 and 12 months.

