#### Primary Outcomes

Changes in knee function and pain were assessed using the OKS questionnaire [22]. OKS is a short, reproducible, valid, and sensitive questionnaire used to assess clinically important changes after TKR surgery [23]. Each of the 12 items was scored from 0 to 4, with 4 being the best outcome. When summed, the overall scores ranged from 0 to 48 points, with higher scores indicating better function and lower knee pain.

The TUG test was used to assess changes in mobility [24]. The TUG test was performed twice at maximum speed, with the shoes on. Time in seconds was measured using a stopwatch. Both results were recorded, and a better result (shorter time in seconds) was used. A lower TUG test time indicated better mobility.

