### Sample Size

The intended sample size (n=100) of the BEE-RCT was based on the primary outcome, the OKS [22]. Assuming a mean difference of 5 (SD 8) points [40] in a change in the OKS between the groups at 6 to 12 months [40,41], a sample size of 42 in the intervention and control groups was required to detect differences between groups at an α of .05 and reach power of 80%. The dropout rate was estimated to be 10%; consequently, a minimum of 100 participants were needed to be recruited. In 2020, the COVID-19 pandemic decreased the number of elective surgeries, such as TKR, and there were lockdowns in exercise laboratories. Due to this, recruitment slowed in the spring of 2020 and was completely stopped for 3 months because of lockdowns. Consequently, the trial failed to recruit the intended sample size of participants.

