### Data Analysis Plan

Repeated measures of the changes in primary and secondary outcomes will be compared between the exergame and standard home exercise groups using intention-to-treat analysis, mixed effects models, and an unstructured covariance structure. Fixed effects included group, time, and group × time interactions. In the primary analysis, repeated measurements will be taken at different time points, including at baseline and at 2 and 4 months. Mixed models allow for the analysis of unbalanced data sets without imputation; therefore, all available data with the full analysis set will be analyzed. In response to the impact of COVID-19, the number of participants is expected to be insufficient for per-protocol analysis. The maintenance of intervention benefits for 12 months will be analyzed using similar mixed effects models as secondary analyses.

A concurrent embedded design of a mixed methods study was used by including a qualitative component within a quantitative study of exercise effectiveness. In the mixed methods approach, quantitative data analysis is mainly descriptive to support the interpretation of qualitative findings. For physical function measures, categorization based on a clinically meaningful level or change from baseline will be used to further integrate the qualitative data. With the qualitative interview data, primarily thematic coding and clustering of the concepts arising from ladder chains are planned [37]. The ladder data will be coded and categorized by 2 researchers and checked until a complete consensus is achieved between them. Integration of quantitative and qualitative data will focus on developing a framework using the identified clusters and structuring them by adopting the interpretative structure modeling technique [42].

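### The article names two unranked primary outcomes (OKS and TUG) but sizes the trial as if OKS were the only one, and does not say how the two combine, so the trial-wide error rate is not fixed

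*Protocol article*

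**What the plan says.** The Abstract (Methods) uses the plural and fixes the time point: "The primary outcomes at 4 months were function and pain related to the knee using the Oxford Knee Score questionnaire and mobility", with mobility measured by TUG. The Primary Outcomes section describes OKS and then adds "The TUG test was used to assess changes in mobility". Neither place ranks the two.

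The Sample Size section uses the singular: the intended sample "was based on the primary outcome, the OKS". Its inputs are for OKS only ("Assuming a mean difference of 5 (SD 8) points" in the change score, alpha .05, 80% power), and it arrives at "a sample size of 42 in the intervention and control groups". No effect size, SD or power is given for TUG.

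The Data Analysis Plan handles all outcomes together: "Repeated measures of the changes in primary and secondary outcomes will be compared between the exergame and standard home exercise groups". It specifies the model, the covariance structure, the time points and the analysis set. It gives no significance level for the tests, no order of testing, and no statement of whether one or both primary outcomes must succeed. The hypothesis under Objectives speaks generally of function and symptoms and is not tied to either measure.

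**The concern.** The article defines the primary outcome in two ways, as a pair in the Abstract and Primary Outcomes section and as OKS alone in the Sample Size section. The stated alpha and power describe a trial with one decisive test. With two primary outcomes, what those figures mean for the trial's claim depends on a success rule that the article does not give.

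A split result, with one primary outcome significant and the other not, is a realistic possibility. The trial is open-label after randomization, enrolled 52 participants against a target of 100, and is described under Strengths and Limitations as probably underpowered. Without a rule, a split result leaves open which outcome carries the conclusion, and that choice could be made after the data are seen.

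**Working it through.** **Inputs from the Sample Size section.** Difference 5, SD 8 (standardized difference 5/8 = 0.625), alpha .05, power 80%, 42 per arm. Whether the test is one- or two-sided is not stated. The correlation between the OKS and TUG test statistics is not given and is assumed to lie between 0 and 0.9. Its sign does not matter for two-sided tests.

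**1. Reproduce the plan's figure.** n per arm = 2 × (1.960 + 0.842)² × (8/5)² = 2 × 7.85 × 2.56 ≈ 40.2, rounded up to 41. The t-test version gives 41.2, rounded up to 42. A one-sided test would need only 32. So 42 per arm is correct for OKS alone at two-sided .05, with power of 80.8% (t) or 81.7% (normal).

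**2. Error if either outcome at two-sided .05 is enough.** With no true effect on either outcome, the chance of a false claim is 1 − P(|Z₁| < 1.96 and |Z₂| < 1.96). For independent tests this is 1 − 0.95² = 9.75%. From the bivariate normal distribution:

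| Assumed correlation | Either outcome significant | Both significant |
|---|---|---|
| 0 | 9.75% | 0.25% |
| 0.3 | 9.51% | 0.49% |
| 0.5 | 9.07% | 0.93% |
| 0.7 | 8.35% | 1.65% |
| 0.9 | 7.04% | 2.96% |

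The last column is 10% minus the middle one. The upper bound for the either-outcome rule is .05 + .05 = 10%.

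**3. Error if both must succeed.** The last column applies when neither outcome has an effect. If exactly one has a real effect, a false claim still requires the other to be significant by chance, which happens at most 5% of the time. The error therefore never exceeds 5%.

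**4. Error if OKS is tested first and TUG only after a significant OKS.** If OKS has no true effect, any false claim requires a chance OKS result, at most 5%. If OKS has a true effect, only TUG can give a false claim, again at most 5%. OKS keeps its full .05, so the calculation in step 1 is unchanged.

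**5. Cost of splitting alpha.** At .025 per outcome, OKS power at 42 per arm falls from 80.8% to 71.9% (t), or from 81.7% to 73.3% (normal). Restoring 80% needs 50 per arm (t) or 49 (normal). Under Holm's procedure OKS is always significant if p ≤ .025, and never if p > .05. At 42 per arm its OKS power therefore lies between 71.9% and 80.8%, depending on how often TUG succeeds.

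**The case against.** The strongest reply is that nothing in the article is shown to be numerically wrong. The only alpha stated belongs to the OKS calculation, and that calculation reproduces. Sizing a trial on one of several primary outcomes is not an error in itself. The text is a journal article that condenses a fuller protocol, and an order of testing or an alpha allocation may well be set out there or in an analysis plan. Most of this stands, and it limits the point in three ways.

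- A reader might infer that each outcome is tested at the full .05 and that the 5% error rate is therefore broken. The documents do not support this. The value .05 appears only in the sample-size statement, no level is given for the analysis, and no either-outcome rule is written. A both-must-succeed rule or a fixed order would keep the error at or below 5%.
- A reader might also want to put a figure on the power for winning on both outcomes. It cannot exceed the OKS power, but any specific value would require an assumed TUG effect and SD, and the article gives neither.
- The planned 42 per arm was not reached. With 52 enrolled (26 per arm if split equally with no losses), OKS power is about 60% to 62% at two-sided .05. The article already concedes low power, so arguing over the planned 80% changes little.

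The reply does not remove the conflict between sections. The same article gives two primary outcomes in one place and one in another, and its own analysis section does not reconcile them. That is an inconsistency in what is stated, not a detail left to another document.

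**Conclusion.** The point holds as an inconsistency with a conditional consequence. Two unranked primary outcomes at 4 months are set against a sample size that treats OKS as the only one, and nothing in the article connects them. The trial-wide error rate is consequently undetermined. It is about 7% to 10% if either outcome at two-sided .05 can carry the claim, and at most 5% if both must succeed or if OKS is tested first. The 7% to 10% range rests on an assumed correlation between the tests of 0.9 to 0 and on an either-outcome rule that the article does not state. The OKS sample size is correct as calculated.

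**What to change.** Before the analysis, make the Abstract, the Primary Outcomes section and the Sample Size section agree, and add the decision rule to the Data Analysis Plan. Suggested content: OKS at 4 months is tested first at two-sided .05. TUG at 4 months is tested as confirmatory at two-sided .05 only if OKS is significant. Otherwise TUG is reported as an estimate with a confidence interval and no confirmatory claim.

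This takes a sentence or two, needs no additional participants, and keeps both the 5% error rate and the stated OKS basis for the sample size. The price is small: TUG cannot support a confirmatory claim if OKS fails. If the investigators want either outcome to be able to succeed on its own, Holm's procedure across the two also controls the error, at the cost in OKS power shown in step 5. Whichever rule is chosen should be dated and recorded before results by group are seen.

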**Results:**

This study was funded in 2018. Data collection began in 2019 and was completed in January 2022. The COVID-19 pandemic caused an unavoidable situation in the study for recruitment, data collection, and statistical analysis. As of November 2020, a total of 52 participants had been enrolled in the study. Primary results are expected to be published by the end of 2022.

**Conclusions:**

Our study provides new knowledge on the effects of postoperative exergame intervention among older patients with TKR. In addition, this study provides a new understanding of gamified postoperative rehabilitation, home exercise adherence, physical function, and physical activity among older adults undergoing TKR.

**Trial Registration:**

ClinicalTrials.gov NCT03717727; https://clinicaltrials.gov/ct2/show/NCT03717727

**International Registered Report Identifier (IRRID):**

RR1-10.2196/38434

## Introduction

### Background and Rationale

People with osteoarthritis (OA) often remain sedentary after total knee replacement (TKR) [1,2], predisposing them to noncommunicable diseases and disabilities with advancing age. Exercise is a recommended core treatment in the clinical guidelines for musculoskeletal disorders and a cornerstone of standard care for patients with OA [3,4]. People with knee OA should follow similar doses of exercise (frequency, intensity, time, type, volume, and progression) as physical activity (PA) recommended by public health authorities to have a positive effect on physical function [5]. Although engagement in PA is difficult for the general population, it is even more challenging for people with OA. They are often physically inactive and highly sedentary because of pain and disease progression [6].

Typically, TKR surgery is performed after years of progressive pain, swelling, stiffness, and decreased range of motion in the joint. The rate of TKRs for severe OA is increasing substantially [7,8], and it is one of the most frequently performed elective surgeries [9]. Fast tracking for TKR involves optimizing the treatment protocol to reduce the primary treatment period and thus reduce the use of institutional care [10]. The primary treatment period after TKR was approximately 3 days, and for 75% of the patients, the discharge destination was home [10]. Emphasis is placed on providing postoperative physiotherapy in hospitals to enable the patient’s independence in activities of daily living (ADL) before discharge. In addition, hospital physiotherapists supervise active home exercises to improve knee range of motion, muscle strength, and weight-bearing while walking. High-intensity outpatient physical therapy directly after discharge improves the functional performance of patients who had undergone TKR [11]. Nonetheless, rehabilitation after discharge is mainly the patient’s responsibility.

A study by Valtonen et al [12] found that although the operation reduces pain effectively, even 10 months after the knee replacement surgery, the knee extension torque and power in the operated lower limb remained weaker than those in the nonoperated side. This asymmetry limits patients’ ability to negotiate stairs [12]. Questionnaires administered to patients 5 years after TKR have shown that their expectations regarding postoperative PA were not fulfilled to the same extent as their expectations regarding pain relief [13]. PA levels remain below the recommended levels, and sedentary behavior continues after TKR [1]. However, meeting preoperative expectations is a significant determinant of overall patient satisfaction following lower limb joint arthroplasty [14].

In the long term, PA would be crucial for the aging population undergoing TKR by reducing the risk of chronic noncommunicable diseases and disabilities in ADL. Exercise adherence is an essential predictor of the long-term effectiveness of exercise therapy both within and after the intervention period [15]. Gamified exercise, or exergaming, is a new approach to increase exercise adherence. Increased exercise adherence using exergames has been reported in several studies involving different patient groups [16,17].

### Objectives

This study explored the effectiveness of home-based exergame rehabilitation on physical function and symptoms after TKR. This “Gamification in Knee Replacement Rehabilitation, randomized controlled trial” (BEE-RCT) is part of the “Business Ecosystems in Effective Exergaming” (BEE) project. The primary objective of this study was to examine the effectiveness of a 4-month gamified home exercise program on physical function, disability, and symptoms following TKR surgery. We hypothesized that people assigned to the exergame arm would have better functional status and lower levels of symptoms than those assigned to the standard home exercise arm.

Furthermore, we will assess exercise adherence and game experience in the gamified home-based rehabilitation arm of the study following TKR surgery and the maintenance of intervention benefits 1 year after TKR surgery. In addition, using a mixed methods approach, we aim to investigate the complex interrelationship between gamified rehabilitation, exercise adherence, PA, physical function, and symptoms in older adults after TKR surgery.

## Methods

### Trial Design

This was a 4-month dual-center, two-arm, parallel group randomized controlled trial that determined the effectiveness of exergame-based home-based rehabilitation by comparing it with standard home exercise after TKR. The 4-month intervention period was followed by the 8-month follow-up period. Participants’ perspectives on rehabilitation and exergames were explored using an embedded qualitative approach. Figure 1 illustrates the flow of this study.

Figure 2 presents the enrollment schedule, interventions, outcome assessments, and interviews. The participants’ functioning, disability, and symptoms were assessed preoperatively *at t_0_* (baseline) and postoperatively *at t_1_*, *t_2_*, *and t_3_* (2nd, 4th, and 12th month, respectively). Individually arranged assessments were conducted in the exercise laboratory at the Turku University of Applied Sciences and the exercise laboratory at the University of Jyväskylä. Research data were collected before TKR surgery at baseline and during the RCT intervention and follow-up periods. The baseline assessment (*t_0_*) was performed within 2 weeks before the planned day of surgery. During the baseline assessment visit, participants provided written informed consent, after which the research physiotherapist measured the outcomes, performed randomization, and guided home exercising according to the allocation group. The postoperative assessments (*t_1_,*
*t_2_*, and *t_3_*) were performed within +5 or −5 days of the postoperative 2-, 4-, and 12-month time points. During the postoperative assessment visit, the research physiotherapist measured the outcomes (*t_1,_*
*t_2_*, and *t_3_*) and guided the PA of standard care and the gym work out for strength training (*t_2_)*.

**Figure 1 figure1:**
[figure not shown]
Flowchart of the Gamification in Knee Replacement Rehabilitation, randomized controlled trial. TKR: total knee replacement.

**Figure 2 figure2:**
[figure not shown]
The schedule of enrollment, interventions, assessments, and interviews in the Gamification in Knee Replacement Rehabilitation, randomized controlled trial.

### Study Setting

The study participants were Finnish patients with knee OA who lived in the Southwest and Central Finland Health Care Districts and had undergone TKR surgery at the Turku University Hospital in the City of Turku or the Central Finland Hospital in the City of Jyväskylä. These hospitals perform approximately 1700 (Turku, 1200 and Jyväskylä, 500) knee joint arthroplasties per year. After discharge from the hospital, patients performed therapeutic exercises independently in their homes for 4 months with either exergame (intervention group) or standard postoperative exercises (control group). The intervention group participants followed the standard postoperative home exercise program when they could not use exergames, such as during vacations in another locality or abroad. For 1 year after surgery, the participants maintained a record of PA.

### Eligibility Criteria

The study participants were men and women aged 60-75 years who had undergone TKR surgery. They were recruited during their preoperative outpatient visits at the Turku University Hospital and Central Finland Hospital. Inclusion criteria for enrollment in the study were as follows: (1) aged 60 to 75 years; (2) first primary, unilateral TKR; (3) diagnoses of primary knee arthrosis (International Classification of Diseases 10th Revision codes M17.0 and M17.1); (4) mechanical axis of the limb in varus; (5) model of the TKR is posterior stabilizing or cruciate-retaining prosthesis; and (6) normal vision with or without eyeglasses. The exclusion criteria were as follows: (1) diagnosed memory disorder or cognitive impairment; (2) neurological conditions (such as Parkinson disease, multiple sclerosis, or stroke); and (3) fractures, rheumatoid arthritis, or other biomechanical disruptions in the affected lower limb within 1 year before surgery. Inclusion criterion for age was set to have a sample presenting a vast majority of patients who had undergone TKR without trauma background or increased number of comorbidities and to control high variability in skills of technology use.

### Recruitment

During the preoperative outpatient hospital visit, the surgeon, with either a physiotherapist or a research nurse, assessed the eligibility of study patients. If a patient was eligible, a physiotherapist or research nurse described the study to the patient and asked for written permission for the research’s initial preoperative contact. The patient was informed of the study course during the initial phone contact. The date of the preoperative baseline assessment was agreed upon by interested patients who did not report conditions that could affect the safety of physical testing and exercise. These conditions included chest pain during exercise or other physical exertions, excessive shortness of breath, cardiac medication, seizures or unconsciousness, fainting, or dizziness. In the baseline assessment, eligibility was reassessed based on the initial survey. The patient provided written informed consent to participate in the study if eligible.

### Random Allocation

After the preoperative baseline measurements, the study participants were randomly allocated one by one to the exergame and standard home exercise groups. A person unrelated to the study had previously used a computer-generated randomization procedure using blocks of 2 and 4 in random order and according to the place of recruitment (Jyväskylä or Turku), gender and baseline Timed Up and Go (TUG) test with time ≤10 seconds (indicating faster performance in patients who had undergone TKR [18,19]). A person unrelated to the study had concealed group allocation cards in opaque sealed envelopes into 4 separate sets of stratification (slow men, slow women, fast men, and fast women) per place of recruitment. After the baseline measurement of each participant, the research physiotherapist of the exercise laboratory opened the next envelope from the appropriate set of envelopes, complying with the allocation stratification, and assigned the participant to the exergame or standard home exercise group according to the group allocation card in the envelope.

